### Sample size

Progression criteria related to feasibility outcomes were identified. We plan to recruit 60 participants (30 in the control group and 30 in the intervention group) in line with sample sizes for similar feasibility studies
^
34
^. Feasibility studies need to be much smaller than full-efficacy trials to be considered worthwhile. The feasibility outcome “participant retention” is the percentage of 60 participants who complete outcome measurements at 12 weeks. Using a binomial probability confidence interval (CI) calculator with a sample size of 60, the 95% CI on proportions will have widths no greater than 37% (based on the 50% proportion having a 95% CI from 37% to 63%. Proportions further from 50% would have narrower CIs; for example, 90% has a 95% CI from 79–96%, so this CI has a width of 17%.
Free Binomial Probability Confidence Interval Calculator - Free Statistics Calculators (danielsoper.com)

The width of these CIs provides a reasonable balance between the cost and practicality of patient recruitment. The feasibility outcome “recruitment uptake” would have narrower CIs (since 60 is the numerator with a larger denominator). There is no relevant power calculation because the main outcomes are proportions rather than anything that can be assessed using hypothesis testing.

The progression criteria targets are described in
Table 4. They provide a guide through the use of a predefined traffic light system of red (stop), amber (amend, modifications needed), and green (proceed), as to whether the study could proceed to a future definitive trial. The targets may seem ambitious, but due to the limited number of appointments and personalised nature of the intervention, where participants do not need to attend appointments at the hospital, we believe these are achievable. We have carried out extensive work with diverse community groups that has improved our understanding of culturally appropriate ways to approach patients from different communities. Further, this is also a single-centre study, with the lead researcher having established working relationships with the other members of the stroke team.

**Table 4. T4:** Progression decision criteria.

FEASIBILITY OBJECTIVES	MEASURES USED	DENOMINATOR FOR PERCENTAGE	GREEN Proceed to full scale trial	AMBER Amendments needed	RED Definitive trial unlikely to be feasible
1. Recruitment uptake	% of eligible people agreeing to take part	Over 60 (numerator is 60)	≥90%	60–89%	<60%
2. Treatment adherence	% of participants that attend both follow-up appointments	30 (patients recruited into treatment arm)	≥90%	60–89%	<60%
3. Participant retention	% of participants that complete outcome measures at 12 weeks	60 (all recruited patients)	≥90%	60–89%	<60%

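### The sample-size section states a maximum 95% CI width of 37% at n=60, but its own limits are about 26 points apart, and it gives no precision for adherence (n=30)

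*Protocol article*

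**What the plan says.** The Sample size section plans 60 participants, 30 per arm. It points to the size of similar feasibility studies and then argues from precision. The calculation is set up as "Using a binomial probability confidence interval (CI) calculator with a sample size of 60". The outcome it is tied to is retention: "The feasibility outcome “participant retention” is the percentage of 60 participants who complete outcome measurements at 12 weeks".

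The headline is "the 95% CI on proportions will have widths no greater than 37% (based on the 50% proportion having a 95% CI from 37% to 63" per cent. A second example follows: "90% has a 95% CI from 79–96%, so this CI has a width of 17" per cent. On uptake the section says: "The feasibility outcome “recruitment uptake” would have narrower CIs (since 60 is the numerator with a larger denominator". It then judges these widths an acceptable compromise and says that no power calculation applies.

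Table 4, in the same section, sets three progression criteria: uptake, adherence and retention. All use the same bands: green at 90% or more, amber at 60–89%, red below 60%. The denominator for adherence is "30 (patients recruited into treatment arm"). The precision text does not mention adherence.

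**The concern.** The headline width contradicts the limits it is said to rest on. An interval from 37% to 63% has 37% as its lower limit, not as its width. With no power calculation, the interval widths are the only quantitative argument for 60 participants, so the figure should be right.

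The paragraph also speaks to two of the three progression criteria and then calls the widths acceptable. The one left out has half the denominator and the widest interval. The only example at the green threshold (90%, 79–96%) is for n=60. It does not describe what 90% adherence would look like on 30 patients.

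**Working it through.** **Inputs.** All are from the Sample size section and Table 4: n=60 for retention, n=30 for adherence, 95% two-sided confidence, worked proportions of 50% and 90%, and a green threshold of 90%.

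**Meaning of width.** In the second example, 96 − 79 = 17, which is the width stated. So width means upper limit minus lower limit. Applied to the first example, 63 − 37 = 26, not 37.

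**Formula.** The exact (Clopper-Pearson) interval for x out of n is:

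- lower limit = 2.5% quantile of Beta(x, n − x + 1)
- upper limit = 97.5% quantile of Beta(x + 1, n − x)

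**Reproducing the plan's figures, then adherence.**

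| x/n | Proportion | Exact 95% CI | Width (points) | Plan states |
|---|---|---|---|---|
| 30/60 | 50% | 36.8–63.2% | 26.4 | 37–63%, width 37% |
| 54/60 | 90% | 79.5–96.2% | 16.7 | 79–96%, width 17% |
| 15/30 | 50% | 31.3–68.7% | 37.4 | nothing |
| 18/30 | 60% | 40.6–77.3% | 36.7 | nothing |
| 27/30 | 90% | 73.5–97.9% | 24.4 | nothing |

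The plan's limits for both n=60 examples reproduce, and so does its 17-point width. Only the 37% does not. Taken over every possible x, the maximum exact width is 26.4 points at n=60 and 37.4 points at n=30.

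**Does another method give 37 at n=60?** No. The maximum widths are:

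| Method | n=60 | n=30 |
|---|---|---|
| Exact | 26.4 | 37.4 |
| Wald | 25.3 | 35.8 |
| Wald, continuity-corrected | 27.0 | 39.1 |
| Wilson | 24.5 | 33.7 |

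By hand, the Wald width at 50% is 2 × 1.96 × √(0.25/60) = 0.253 for n=60 and 2 × 1.96 × √(0.25/30) = 0.358 for n=30.

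**The remark on uptake.** It holds. With 60 recruited out of 120 eligible (50%) the exact width is 18.5 points, against 26.4 for 30/60. With 60 out of 67 (about 90%) it is 16.0, against 16.7 for 54/60. The 120 and 67 are illustrative denominators, not figures from the protocol.

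**Dependence on arm size.** The Randomisation section specifies simple randomisation, stratified by recruitment location, which does not by itself guarantee 30 per arm. At 50%, the exact width is 38.7 points with 28 in the arm and 40.1 points with 26.

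**The case against.** Several things can fairly be said for the plan.

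- The correct limits stand in the same sentence, so a careful reader can see the slip. Read literally, a bound of 37% is still true at n=60, only loose. That stands as far as it goes. But the text says the figure is based on the 37–63% interval, and that interval gives 26. It is a wrong derived number, not a chosen conservative bound.
- The precision text is explicitly about n=60 and makes no claim about adherence. Table 4 shows the denominator of 30 openly, and the Statistical methods section commits to reporting the feasibility outcomes as proportions with confidence intervals. This stands: the adherence part is an omission, not a false statement. It is still worth closing, because the section goes outcome by outcome, skips the least precise one and then draws a conclusion about adequacy.
- Table 4 classifies on observed percentages and is described as a guide. No rule uses a confidence limit, so no red, amber or green result changes. This stands too.

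Some stronger readings are tempting, but the document does not support them. A reader might infer that 60 is too few for retention; the error runs the other way, since true precision is better than stated. A reader might infer that the whole case for 60 rests on the wrong figure; the section also relies on similar feasibility studies and on practicality. A reader might infer that the 37% is an n=30 result carried over, because 37.4 is the n=30 maximum; it could equally be the lower limit copied as the width, and the document does not show which. Finally, the plan nowhere applies 79–96% to adherence.

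**Conclusion.** Wrong as written, and minor. The maximum 95% CI width at n=60 is 26.4 points by the exact method, or 24.5 to 27.0 across the four methods tried. The stated 37 overstates the width by about 11 points (37 − 26.4 = 10.6) and so understates precision.

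The omission concerns adherence. If 30 participants are allocated to the intervention arm, its exact interval is up to 37.4 points wide. That width applies near 50%. At 27/30, exactly on the green threshold, it is 24.4 points, with a lower limit of 73.5%, well inside the amber band. The n=60 example at 90% has a lower limit of 79.5%.

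The verdict on the 37% needs only the plan's own two limits. The adherence figures assume the exact method, which reproduces the plan's limits, and an arm of 30.

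**What to change.** Replace the sentence on maximum width, and the 90% example after it, with wording such as:

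> For retention (n=60) the exact 95% CI will be at most about 26.4 percentage points wide (50%: 37–63%; 90%: 79–96%). For treatment adherence, if 30 participants are allocated to the intervention arm, it will be at most about 37.4 points wide (50%: 31–69%), and about 24 points wide at the 90% green threshold (27/30: 73–98%). It will be somewhat wider if fewer than 30 are allocated.

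The remark on uptake can stay. The cost is a few lines of text and a less favourable stated precision for adherence. The sample size, Table 4 thresholds, conduct and analysis do not change. Recruitment is closed according to the Trial status section, so the practical use of the correction is in how the progression results are read and reported.

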### Withdrawals of participants

It will be made clear to all potential participants through the consent form and discussions that they are free to withdraw from study participation at any point, and that they are not required to provide a reason for this.

### Intervention

The intervention is a personalised, holistic follow-up programme of care. It has been developed for a diverse population with differing stroke aetiologies and social contexts and for this reason was guided by the NIHR/MRC framework for complex interventions
^
18
^ alongside the framework of actions developed by O’Cathain and colleagues
^
35
^. The behavioural theory chosen to underpin this intervention is self-determination theory (SDT). This theory aims to increase autonomous motivation, which has been shown to be associated with improvements in initiating and sustaining healthy behaviours
^
36–
38
^. The techniques described by SDT aim to support a person’s three basic psychological needs for competence, autonomy, and relatedness
^
39
^. It highlights the importance of considering a person’s biological, social, and cultural contexts, which is critical given the diversity of the stroke population. The follow-up appointments will address knowledge gaps, provide support, education, guidance, signposting, and onward referrals as needed. A detailed description as per the TIDieR guidelines for the intervention and control groups is provided in the Open Science Framework (OSF) data repository.
https://osf.io/gnw57/

The hypothesized mechanisms for action of the intervention are underpinned by self-determination theory and are:

1)
**Enhanced, personalised communication** – this requires listening to and understanding the participants priorities and needs. It requires an understanding of a person’s health literacy and education level. Communication is personalised and adjusted according to the participants needs.

2)
**Partnership working** – this approach changes the power dynamic in healthcare interactions and moves away from traditional hierarchical, paternalistic approaches and facilitates the pursuit of personalised goals. It involves linking the participant in with or referring them on to other support services in the community. This approach helps to address adjustment to life after stroke and can mitigate against feelings of isolation and abandonment. It aims to support a sense of belonging, feeling cared for and connected with others.

3)
**Enablement** – by focusing on communication and partnership working a participant is supported to have freedom of choice to engage in actions that are congruent with their values and priorities. They are given the tools and knowledge to influence the outcomes that are important to them. This supports intrinsic motivation to initiate and sustain behaviour that supports health and wellbeing.

### Materials and procedures

A training manual for those delivering the intervention has been developed and can be found in the OSF data repository in the intervention delivery folder, accessed here:
https://osf.io/gnw57/

The manual describes the principles of SDT and how the techniques can be employed during follow-up appointments. It also describes the key knowledge and skills that are required by the person delivering the intervention and outlines the domains of functioning to be covered in the assessment conducted at the follow-up appointments. Topic areas for discussion in each follow-up appointment are listed, and guidance is provided when onward referrals are needed. Links to relevant informational resources that the participant may require are included in this manual, as well as what to consider if referring to local community stroke services. An intervention delivery checklist has been created to check off all the actions that need to be taken from recruitment through to outcome measurement at 12 weeks. This is also available in the extended data.

The participants GP will be informed of their involvement in the study and which group they have been randomised to. A brief description of the purpose of the study and what it involves, as well as the researcher’s contact details will be included in the letter sent to the GP.

### Intervention provider

For this feasibility study, the lead researcher, who is an experienced stroke occupational therapist, will deliver the intervention. The intention, however, is that this intervention could be delivered by other allied health professionals (AHPs) or nurses with experience working with the stroke population. Therefore, the training manual is designed to address the training needs of both nurses and AHPs. This will be reviewed by nurses and AHPs to obtain feedback on the content, layout, and general utility in supporting delivery of the intervention.

### How, when and where

The mode of delivery of the intervention will focus on inclusivity. To ensure the delivery of a personalised intervention, follow-up appointments will be offered face-to-face in person at the hospital, participant’s home, or a neutral venue in the community, or as a telephone or video call appointment. Participants will have the option of completing their twelve-week outcome measurement in person or alternatively electronic versions of the outcome measures will be sent to participants for their completion. The preferred modality will be noted and will inform a future definitive trial. Where signposting to online information resources or digital Apps is indicated this will form part of the intervention. This will however only be utilized with those that are familiar with and have easy access to these technologies.

The intervention is composed of two follow-up appointments and telephone access to the researcher to address questions that may arise between appointments. The researcher has direct access to the clinical team and stroke clinical specialist nurses if medical concerns are raised. This may help to address feelings of abandonment that are frequently described in the literature. Currently it is very difficult to have ad hoc contact with the stroke clinical team after discharge. Participants in this group will receive referral to the Stroke Association Connect Service and six-month stroke review referrals as part of standard care. The formal follow-up appointments will occur at 2 and 6 weeks after recruitment and will last from 30 to 60 min, depending on the identified needs.

Appointment 1 (two weeks after discharge):

-Understand the participant’s priorities and expectations for the appointment.-Review functional and psychosocial status. This will provide information on the early impact of stroke, determine what support the participant has in the community, and provide insights into how they are adjusting to their new diagnosis.-Address the participant’s knowledge gaps regarding stroke, medication, and secondary prevention.-Agree onward referrals if indicated and action plan for participant and clinician.-Written summary sent to GP with topics discussed and action plan agreed.-Summary of discussion points provided to participant when required or requested.-Complete an early post-stroke quality of life measure (patient-reported outcome measurement information system, PROMIS10)

Appointment 2 (six weeks after discharge):

-Understand the participant’s priorities and expectations for appointment.-Review actions from first appointment.-Address any new or persistent information gaps.-Review functional and psychosocial status, with a focus on potential hidden impairments that may impact return to work, activities of daily living, relationships, or general well-being.-Agree onward referrals and action plan.-Summary of discussion points provided to participant when required or requested.-Written summary and plan to be sent to GP with topics discussed and action plan agreed.

Examples of onward community-based referrals that may be needed include referral to the community stroke therapy team. This may be highlighted when the person is back at home and engaging in their everyday activities and they then become aware of higher-level difficulties that were not detected initially. The hidden impacts of stroke such as fatigue and mood issues are also more likely to become apparent after a period of time at home. The UK and Ireland National Clinical Guidelines for Stroke (2023) now support the need for referral for ongoing rehabilitation at any time point after a stroke if new goals are identified. Other referrals to voluntary sector organisations for information, peer support or exercise groups can also be made if indicated.

**
*Tailoring*
**

The content and direction the appointment takes is guided by the manual, but will be tailored by the participant’s own priorities, knowledge gaps, and functional difficulties experienced since their stroke. Information delivery will be tailored to general literacy and health literacy. The participants’ family members or partners will be able to join follow-up appointments if they wish.

**
*Baseline and outcome measurement*
**

Baseline measures for both groups will be conducted by the OT in the hospital where possible, but if the person is discharged quickly or seen in the RAC, then they will be conducted at the persons home or in the clinic. Baseline assessment will be conducted within one week of the stroke. The location of the final outcome measurement will be agreed upon by the participant and could be in their home or in the hospital.

Measurement will be taken by the OT delivering the intervention. Participants will be invited to participate in qualitative interviews after the 12-week outcome measurement period.

**
*Control group*
**

The participants in the control group will receive standard care. This involves the provision of a printed information sheet on therapy services that exist in their locality and referral to the Stroke Association Connect service, which makes telephone contact with the person after discharge. A six-month stroke review referral is also sent, but currently, this is not consistently provided across all localities. In addition to standard care, those in the control group will be provided with a mobile number and email address for the lead researcher to enable easy contact during the 12-week duration of the study if questions arise relating to their stroke or its effects. If referrals onto community stroke therapy services are indicated at the 12-week outcome measurement appointment then they will be made at that time.

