### Trial design

The current trial is a two-armed, parallel group, randomised, single-center, feasibility study with embedded qualitative interviews. Participants and the outcome assessor, a specialist occupational therapist (OT), will not be blinded to the intervention. The study flowchart is shown in the Consort Diagram
Figure 1.

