### Secondary feasibility outcomes

1. To complete patient reported outcome measures and review their acceptability, accessibility, and responsiveness to inform the primary outcome for a main trial.

i.PROMIS10 - Patient-reported outcome measurement information system. This quality-of-life measure was chosen because it has been found to be more sensitive in people who have mild strokes
^
40,
41
^ (T1 and T4). ii.HCCQ - Health Care Climate Questionnaire Short Form – This is a measure of self-determination, particularly autonomy support in health care appointments
^
42
^ (T0 and T4).iii.PHQ9 – Patient Health Questionnaire – measure of depression
^
41,
43
^ (T4).iv.GAD7 – Generalised Anxiety Disorder – measure of anxiety
^
44
^ (T4).v.PEI - Patient Enablement Instrument – measures whether an appointment with a healthcare practitioner impacts a person’s ability to manage their illness
^
45
^ (T4).

2. To assess stroke knowledge, questions used relate to information that should be provided to patients in their personal stroke record available at:
https://www.stroke.org.uk/sites/default/files/professionals/jn_2223-055_-_personal_stroke_record.pdf This document (patient passport) was developed by the Stroke Association in collaboration with stroke survivors, their families, clinicians, and NHS England. The stroke knowledge questions that will be asked are:

i.What type of stroke did you have?ii.What treatment have you had for your stroke?iii.Where in your brain did the stroke happen?iv.How has your stroke affected you?v.How can you reduce your risk of another stroke?vi.What new medication are you on?vii.What are the medications for?viii.What should you do if you experience symptoms of another stroke?

3. To complete the cognitive screening assessment, the Montreal Cognitive Assessment
^
46,
47
^ (MoCA) will be conducted in person where possible otherwise over the telephone or video call (T-MOCA
^
48
^) (T0 and T12).

4. To determine the feasibility of gathering self-reported health and social care usage data (attendance at GP and A&E for stroke-related concerns and new packages of care).

5. To complete qualitative interviews (T5).

6. To determine treatment costs based on appointment, administration and travel time.

7. To note which mode of follow-up is most preferred by participants and whether outcome measures can be effectively completed over the telephone.

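### HCCQ and PEI, which concern health care appointments, may be answered at 12 weeks to the OT who gave the intervention appointments, so their between-arm contrast is at risk of courtesy bias

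*Protocol article*

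**What the plan says.** All references are to the protocol article.

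- **Provider.** Under Intervention provider, "the lead researcher, who is an experienced stroke occupational therapist, will deliver the intervention".
- **Collector.** Under How, when and where (Baseline and outcome measurement), "Measurement will be taken by the OT delivering the intervention".
- **Blinding.** Under Trial design, "Participants and the outcome assessor, a specialist occupational therapist (OT), will not be blinded to the intervention".
- **Content of the scales.** Secondary feasibility outcomes says of HCCQ: "This is a measure of self-determination, particularly autonomy support in health care appointments". It is taken at T0 and T4. PEI "measures whether an appointment with a healthcare practitioner impacts a person’s ability to manage their illness" and is taken at T4 only.
- **Mode at 12 weeks.** In person or, as an alternative, "electronic versions of the outcome measures will be sent to participants for their completion" (How, when and where). Item 7 of Secondary feasibility outcomes also foresees completion by telephone.
- **Use.** Statistical methods judges responsiveness by confidence intervals for change within each group and for the between-group comparison of changes. It lets the results inform the primary outcome of the definitive trial. It concedes that the assessor is unblinded and plans a blinded one for that later trial.

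**The concern.** The caveat in Statistical methods covers an assessor who knows the allocation. It does not cover an assessor whose own appointments are the natural subject of the answers. A participant who has had two appointments with the OT, and is then asked by that OT how supportive or enabling appointments were, has a reason to be generous. A control has less reason, because the OT gave that person no follow-up appointment.

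The other patient-reported scales do not share this feature in the same form: PROMIS10, PHQ9 and GAD7 are described as measures of the participant's own quality of life, depression and anxiety.

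What is at stake is the choice of primary outcome for the definitive trial. A difference produced by politeness would look like responsiveness. HCCQ is also the scale tied most closely to the theory behind the intervention, so a favourable result on it would be persuasive.

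**Working it through.** **1. Contact with the OT, arm by arm**

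| Contact | Intervention | Control |
|---|---|---|
| Baseline measurement | yes | yes |
| Appointments at 2 and 6 weeks | two | none |
| Telephone access between visits | yes | yes, and email |
| 12-week measurement | yes, unless done electronically | yes, unless done electronically |

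(Sources: How, when and where, including Baseline and outcome measurement and Control group.) The arms differ in one row, and that row is the kind of encounter the two scales are described as being about. This asymmetry gives the likely direction of the bias, in favour of the intervention.

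**2. Which comparison each scale allows**

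HCCQ has T0 and T4 values, so the planned comparison of changes applies. PEI has no baseline (Table 5; Secondary feasibility outcomes), so it can only be compared between arms at T4. For PEI, the contrast exposed to courtesy is the only between-arm evidence there is.

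**3. Size, as an illustration only**

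The protocol gives no SD, effect size or bias for either scale, so it has no figure to reproduce. Inputs: 30 per arm (Sample size) and 90% retention (the green threshold in Table 4), so n = 0.9 × 30 = 27 per arm. The bias b, in SD units of the quantity compared, is assumed.

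- SE of the difference = √(2/n) = √(2/27) = 0.272 SD.
- 95% interval half-width = t(0.975; 52) × 0.272 = 0.55 SD.
- Coverage = Φ(1.96 − b/SE) − Φ(−1.96 − b/SE).

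| Assumed bias, all intervention completers | b/SE | Coverage of the 95% interval |
|---|---|---|
| 0 | 0 | 95% |
| 0.2 SD | 0.735 | 89% |
| 0.5 SD | 1.84 | 55% |

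With no true effect, 100% minus coverage is the chance that the interval excludes zero: about 11% at 0.2 SD and 45% at 0.5 SD, against 5% without bias.

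The table applies the bias to every intervention completer, whereas the mechanism works only on forms completed with the OT. If half were completed electronically (assumed), the average bias would be 0.1 to 0.25 SD, b/SE would be 0.37 to 0.92, and coverage would be about 93% and 85%.

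**The case against.** The strongest reply is that this is largely disclosed. The dual role is stated openly, the assessor is declared unblinded, and the resulting bias is conceded. These are secondary outcomes of a feasibility study without an efficacy test, Table 4 uses neither scale, and the primary outcome will be chosen on acceptability, perceived relevance and interviews as well as numbers. All of that stands and limits the weight of the point. It does not remove it, because the caveat is about knowledge of allocation and not about answering to the provider.

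Four stronger readings are tempting and are not supported:

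- **Participants score the OT personally.** Item wording is not shown; the protocol says only that the scales concern appointments.
- **Controls have nothing to report on.** They may have routine medical follow-up, they meet the OT for measurement, and they can telephone or email. Which appointment they should have in mind is detail that an article may leave to the full protocol or the forms.
- **Courtesy acts in one arm only.** Controls know the OT too; exposure is unequal, not absent.
- **The comparison is biased.** Only a risk can be shown. Electronic completion is already an option, and no document gives the share that used it.

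There is also a practical objection. Recruitment is closed and outcome measurement is under way (Trial status). The amendment that added PEI was submitted on 01/11/2023 and approved on 06/02/2024, which is 97 days, against a 12-week (84-day) follow-up. If a similar amendment were needed, few or no 12-week visits might remain. In that case only the reporting part of the fix applies. Patient input also reported difficulty completing measures on a mobile phone, so electronic completion cannot be the only private route.

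**Conclusion.** The point holds as a risk of bias specific to HCCQ and PEI. Answers about appointments may be given to the person who delivered them, and the arms differ in exposure to that person. The likely direction favours the intervention. The size cannot be derived from the documents; the coverage figures of 89% and 55% rest on an assumed bias of 0.2 and 0.5 SD in all intervention completers with 27 per arm, and shrink as more forms are completed privately. The feasibility outcomes and progression criteria are untouched. What is affected is the use of these two between-arm contrasts in choosing the definitive trial's primary outcome.

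**What to change.** **For 12-week assessments still to come**
- Have HCCQ and PEI self-completed in both arms out of the OT's sight, by the existing electronic form or on paper sealed in an envelope at the visit, with family help where needed.
- Keep the HCCQ wording used at T0. A new question stem at T4 would break the change score.
- Record the mode actually used and who helped. The article plans to note only the preferred mode.

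**For forms already completed with the OT**
- Report the two scales by mode, descriptively only, because participants chose their mode.
- Do not treat the between-arm difference as evidence of responsiveness when choosing the primary outcome.
- Compare PEI at T4 only.

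**Cost.** An instruction to participants, envelopes and two data fields; no extra staff. Expect some extra missing items on two secondary scales. Where baseline HCCQ was completed with the OT, the within-group change will also carry a change of mode, which should be stated. The remaining measures can be taken at the visit as planned.
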